
### Data analysis

#### Sample size determination

As this topic of study is novel, it was assumed that a previously published study investigating the effect of ginger on pain relief in women with dysmenorrhea would provide an indication of the required sample size [38]. Abdominal pain scores as measured by the 100-point visual analog scale in the women receiving ginger was 58.01 ± 14.52. After 1 month on the ginger intervention, abdominal pain intensity decreased significantly to 43.49 ± 19.99. In the absence of data to estimate the standard deviation for expected change in pain score for the ginger, the standard deviation (19.99) for the final time point was used for the sample size calculation. A difference of 9 for the change in pain scores between intervention groups would provide an effect size of 0.5, which converts to approximately 69% of the control group to be below the average person in the experimental group [42]. We estimate that 79 participants per group will be required to find a 9-point difference in pain score between the probiotic and placebo with an alpha of 0.05 and 80% power. This sample size should allow for finding significant difference for change in pain scores between groups (i.e., the primary outcome). To account for a 15% drop-out rate, a total of 93 per arm for a total of 186 women will be invited to participate. Participants will be stratified on self-reported abdominal pain related to menstruation into groups of mild abdominal pain (score of 3) and moderate to very severe abdominal pain (score 4-7).

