**Methods and analysis:**

In this randomized, double-blind, placebo-controlled parallel study, participants will receive either a probiotic or placebo supplement. Participants will begin answering questionnaires approximately 7 days before the start of menstruation (i.e., active bleeding), and 3 days later, they will begin consuming the study supplement for 8 weeks. The questionnaires administered will collect data about abdominal pain severity (primary outcome) and duration related to the menstrual cycle, digestive health, dietary intake, stress, and digestion-associated quality-of-life. A subgroup of women will provide weekly vaginal swabs and stool samples to examine the effect of the probiotic supplement on microbiota composition and diversity for exploratory purposes. Two-sided tests using a linear model and a type I error rate of *α* = 0.05 will be employed to test all hypotheses. Continuous variables will be presented as means with standard errors and categorical variables, as counts or proportions.

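### The sample-size section states an effect size of 0.5 (69%), but its inputs give 0.45 (67%); N is right, and the 80% power for the change score depends on an unstated pre/post correlation

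*Protocol article*

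**What the plan says.** All the design figures are in the protocol article under Sample size determination. The planning data come from one arm of a published ginger trial in dysmenorrhea, on a 100-point visual analog scale. Pain at baseline "in the women receiving ginger was 58.01 ± 14.52", and after one month "abdominal pain intensity decreased significantly to 43.49 ± 19.99". The section explains that no SD of the change was available and names its stand-in: "the standard deviation (19.99) for the final time point was used for the sample size calculation". The effect is then described: "A difference of 9 for the change in pain scores between intervention groups would provide an effect size of 0.5". The text turns this into roughly 69% of controls lying below the average treated woman. The result is "We estimate that 79 participants per group will be required to find a 9-point difference in pain score"; the error rate and power attached to it are given as "with an alpha of 0.05 and 80% power". Allowing for 15% dropout gives 93 per arm and 186 in total.

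Study outcomes defines the primary outcome as a change: the mean of the first three days of menstruation 2 minus the mean of the first three days of menstruation 1. Statistical analysis tests that mean change by a t test or a non-parametric equivalent. The Abstract (Methods and analysis), which also sets alpha at 0.05, describes the testing more generally: "Two-sided tests using a linear model and a type I error rate of".

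**The concern.** There are two separate matters.

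First, the effect size, its percentage conversion and the sample size sit in one paragraph but do not belong to one calculation. A reader who checks 79 against the stated 0.5 cannot reproduce it, and the effect the trial is designed to find looks larger in standardised terms than it is.

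Second, the SD describes one follow-up score, while the test is on a difference between two scores. The SD of that difference depends on how strongly the two scores correlate. The 80% power for the primary outcome therefore rests on a correlation that the section neither states nor brackets, although it prints both SDs needed to do so.

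**Working it through.** **Inputs** (Sample size determination unless noted): difference 9; SD used 19.99; baseline SD 14.52; alpha 0.05, two-sided (Abstract); power 80%; 1:1 allocation (Overall design); dropout 15%. The pre/post correlation r is not in the document, so every value of r below is an assumption.

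**1. Reproducing the plan's N.**
- d = 9/19.99 = 0.450.
- Normal approximation: n = 2(1.960 + 0.842)² × 19.99²/9² = 77.4, so 78 per group.
- Two-sample t test: n = 78.4, so 79 per group, with power 80.3% at 79. This is the stated figure.
- Dropout: 79/(1 − 0.15) = 92.9, so 93 per arm and 186 in total. These also match.
- A one-sided test gives 62 (normal approximation), which does not match.

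**2. Testing the stated effect size.**
- With d = 0.5 the t test needs 63.8, so 64 per group. At 79 per group, d = 0.5 would have 87.8% power.
- d = 0.5 would require an SD of 9/0.5 = 18, or a difference of 0.5 × 19.99 = 10.0 points. The section has neither.
- Conversion to the share of controls below the average treated woman: Φ(0.450) = 67.4% and Φ(0.5) = 69.1%. The stated 69% belongs to 0.5.
- So N was computed from 0.45, and the interpretation from 0.5. The overstatement is 0.50/0.45 = 1.11, or 11%.

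**3. SD of the change from the section's own two SDs.**

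SD(change) = √(14.52² + 19.99² − 2r × 14.52 × 19.99) = √(610.43 − 580.51r).

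This equals 19.99 when 14.52² = 2r × 14.52 × 19.99, that is r = 14.52/(2 × 19.99) = 0.363. A higher r makes the SD smaller, and a lower r makes it larger.

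| Assumed r | SD of change | n per group for 80% | Power at 79 per group |
|---|---|---|---|
| 0 | 24.7 | 120 | 62% |
| 0.2 | 22.2 | 97 | 72% |
| 0.3 | 20.9 | 86 | 77% |
| 0.363 | 19.99 | 79 | 80% |
| 0.5 | 17.9 | 64 | 88% |
| 0.7 | 14.3 | 41 | 98% |

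**4. The same N with baseline adjustment.** In a linear model of the menstruation 2 score adjusted for the menstruation 1 score, the residual SD is 19.99 × √(1 − r²), which never exceeds 19.99. Power at 79 per group is then about 80% at r = 0, 82% at 0.2, 84% at 0.3, 90% at 0.5 and 98% at 0.7.

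**The case against.** The strongest reply on the effect size is that 0.4502 is 0.5 to one decimal, that 69% and 67% differ by less than two percentage points, and that neither figure enters the sample size. The last part stands: 9 points, 19.99, 79, 93 and 186 form one coherent chain, and no enrolment number is affected. The rounding defence is weaker, because the rounded value is carried forward into the 69% and cannot be reconciled with 79.

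On the SD, the reply is that the protocol discloses the substitution and gives its reason, and that an article may leave further detail to the full protocol or analysis plan. The disclosure stands, and this is not a concealed assumption. But the section goes on to claim that the sample size is adequate for the change in pain scores, and that claim holds only under a condition on r that the disclosure does not mention.

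Two stronger readings are tempting. A reader might infer that the sample size is wrong, or that 64 per group would have been enough. The figures do not support this, since 79 is correct for the 9-point difference and SD actually used. A reader might also infer that the trial is underpowered. The document gives no correlation, so r = 0 has no more support than r = 0.6, and above about 0.36 the chosen SD is conservative.

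**Conclusion.** The stated effect size and percentage are wrong for the section's own inputs: 0.45 and about 67%, not 0.5 and about 69%. This is certain, needs no outside source, and leaves 79 per group and 93 per arm unchanged.

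The 80% power for the change-score t test is not assured. It holds if the pre/post correlation is at least about 0.36. Over r from 0 to 0.7 it runs from 62% to 98%, so the error could lie in either direction. That range assumes that the ginger arm's two SDs carry over to this trial. They come from a single arm of a study in a different population, and the article does not say whether those scores were three-day averages like the ones planned here. The power figures are for the parametric t test.

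**What to change.** In Sample size determination, restate the effect size as 0.45 and the conversion as about 67%. Leave 79, 93 and 186 as they are.

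Then choose one of two routes for the power statement:

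- **Adjust for baseline.** Change the primary analysis in the Statistical analysis section to a linear model of the menstruation 2 score adjusted for the menstruation 1 score, bring the outcome wording into line, and state that the power refers to that model. This agrees with the linear model in the Abstract and uses data already collected. If the follow-up SD is 19.99, 79 per group gives about 80% power or more at any correlation. Editing the sample-size section alone is not enough, because Study outcomes and Statistical analysis now fix a t test on the change.
- **Keep the t test on the change.** State that the 80% assumes a pre/post correlation of at least about 0.36, and give the power range on both sides of that value.

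The second route costs a few sentences in one section. The first also means amending the primary analysis and the outcome wording. Neither needs more participants. The only loss is a slightly less favourable effect size.

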#### Statistical analysis

Intent-to-treat analyses will be performed for all outcomes with all eligible participants. A compliant per protocol analysis will be conducted on the primary outcome. Participants will be considered compliant if they consume > 80% of the interventional product during the 8 weeks of the study. Since there is only a single outcome measured, no imputation will be performed for missing variables. Statistical models that account for unbalanced data will be used if warranted, to account for participate drop out. Study results will be statistically analyzed by a statistical software programs (SAS and SigmaPlot). The mean delta (difference between pre and post-supplementation) will be tested by parametric or non-parametric *t* test depending on the normality of the data. Continuous variables will be presented as means with standard errors (SEM). Categorical variables will be analyzed as count or proportions. The significance of statistical tests will be determined using a type I error rate cut-off of 0.05. Categorical variable counts and proportions will be reported along with relevant standard errors.

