#### Exclusion criteria

Using a birth control implant, vaginal ring, shot, patch, or IUD;Lactating or known to be pregnant;Currently on treatment for a physician-diagnosed GI or gynecological disease or condition;Experiencing pain that is caused by a disorder of reproductive organs including endometriosis, adenomyosis, uterine fibroid, or a pelvic infection;Use of another investigational product within 3 months of screening;Antibiotics or probiotic supplements consumed within 1 month before screening;Allergy to milk, soy, or yeast.

Participants may withdraw from the study at any time. They are encouraged to contact a study coordinator to withdraw from the study. Some participants may discontinue study activities without notice, in which case they will be consider lost to follow up. The principal investigator may withdraw participants as well if they no longer meet the inclusion and exclusion criteria.

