#### Implementation

After participants provide their informed consent and eligibility is confirmed, they will be assigned a study number based on the order that they consented. Participants will then be assigned to a week to begin the study based on when their next menstrual event occurs. Within each week, participants will be randomized by a co-investigator ([name]) based on the order that they consented. Only the study number will be used during the study to identify participants, and all data will be permanently anonymized after study completion.

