While we will encourage participants to avoid pain relievers, consumption of over the counter pain relievers to assist with the pain associated with the menstrual cycle will be allowed for ethical reasons. We will ask participants to report any pain reliever consumption and instruct them to report their greatest abdominal pain intensity prior to consumption.

A subgroup of 20 participants per arm will also be asked to sign a separate informed consent form which will detail all of the main study tasks and will also include information on providing ten stool and vaginal swab samples during the study (study days − 7, 1, 7, 14, 21, 28, 35, 42, 49, and 56). These participants will be provided with stool and vaginal swab collection kits and receive instructions on how to self-collect these samples at home. Participants will be asked to return the samples to the study site. This subgroup will also complete additional 24-h dietary recalls (study days 1, 42, 49, and 56).

Participants will continue to answer daily questionnaires until the third day of their third menstrual cycle, at which point they will discontinue answering questionnaires and consuming the study supplement. At the conclusion of the study, blinding efficacy will be assessed via a questionnaire asking participants which supplement they thought they were consuming. Participants will be instructed to either return any unused capsules or text a picture of the remaining capsules to the study coordinator for compliance assessment.

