### Study outcomes

The primary outcome is the change in abdominal pain intensity related to the menstrual cycle at the beginning of the menstruation, calculated as the average of the first 3 days of “menstruation 2” when on the intervention minus the average of the first 3 days of “menstruation 1” prior to initiating the intervention. A daily visual analog score will be used to measure abdominal pain intensity between women on the probiotic versus the placebo interventions. We hypothesize that women consuming a probiotic will experience a greater decrease in abdominal pain compared to women on the placebo.

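### The reason given for not imputing is false, the only named primary test is by default a complete-case analysis, and the intention-to-treat set is not tied to all randomised women

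*Protocol article*

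**What the plan says.** The Statistical analysis section of the protocol article makes four statements that bear on this point.

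- Analysis set: "Intent-to-treat analyses will be performed for all outcomes with all eligible participants".
- Missing data: "Since there is only a single outcome measured, no imputation will be performed for missing variables".
- Drop-out: "Statistical models that account for unbalanced data will be used if warranted, to account for participate drop out".
- Primary test: "The mean delta (difference between pre and post-supplementation) will be tested by parametric or non-parametric" t test, the choice depending on normality.

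Other sections matter too. Study outcomes defines the primary outcome as the three-day mean pain score at menstruation 2 "when on the intervention minus the average of the first 3 days of" menstruation 1. Study conduct says: "Participants will continue to answer daily questionnaires until the third day of their third menstrual cycle". The text under Exclusion criteria adds: "The principal investigator may withdraw participants as well if they no longer meet the inclusion and exclusion criteria". Implementation places the eligibility check before allocation: "After participants provide their informed consent and eligibility is confirmed, they will be assigned a study number". The Abstract describes the testing of all hypotheses as two-sided, with a linear model.

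**The concern.** There are three linked weaknesses.

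First, the reason given for not imputing does not describe this trial. Even if there were only one outcome, that would be no reason to leave missing values unaddressed.

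Second, a woman who lacks either menstruation mean has no change score and drops out of the named test. The result is unbiased only if such women would have changed by the same amount as the others, or if any difference cancels between arms. The plan states no such assumption and offers no way to test it.

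Third, the label intention-to-treat is attached to a set defined by eligibility, while another rule allows withdrawal when eligibility lapses. An analyst could therefore remove women for events after randomisation and still use the label. At stake is who enters the primary comparison.

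**Working it through.** **1. The stated reason against the rest of the article.** Statistical analysis speaks of one outcome. The same section promises intention-to-treat analyses for all outcomes. The secondary outcomes list has eight items plus the exploratory microbiota item. The primary change uses 3 + 3 = 6 daily scores per woman, and daily scoring runs on to menstruation 3. The reason cannot be squared with these.

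**2. The plan's own sample size.** Inputs from Sample size determination: difference 9, SD 19.99, alpha 0.05, power 80%, drop-out 15%. Two-sided testing comes from the Abstract and 1:1 allocation from Overall design.

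- Normal approximation: n = 2 × (1.96 + 0.84)² × (19.99/9)² ≈ 77.4, so 78 per arm.
- Two-sample t test version: 78.4, so 79 per arm, as stated.
- Inflation: 79 / (1 − 0.15) = 92.9, so 93 per arm and 186 in total, as stated.

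The design therefore allows for 93 − 79 = 14 women per arm, or 28 of 186, without an analysable change score (0.15 × 186 = 27.9). Power is 80% with 79 per arm and 86% if all 93 contribute. Loss of power at 15% is already budgeted, so what remains is possible bias and the undefined analysis set.

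**3. What the named test does with these women.** A t test on the change tolerates unequal arms but cannot use a woman with no change score. A model for unbalanced data helps only if it works on the repeated scores. If it works on one change score per woman, it is still a complete-case analysis. The article does not say which is meant, or what would make it warranted. The Abstract's linear model is compatible with the parametric t test, which is a special case, but not with the non-parametric alternative.

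**4. Illustrative bias.** Let m be the fraction missing in an arm, and D the mean change in missing women minus that in observed women. The full-arm mean is the observed mean + m × D, so the complete-case comparison is off by m₁D₁ − m₀D₀. All values of D, and the unequal missing fractions, are assumptions. Only the 15% comes from the article.

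| Missing (arm 1 / arm 0) | Gap D (arm 1 / arm 0) | Error in points | Share of the 9-point target |
|---|---|---|---|
| 15% / 15% | 5 / 0 | 0.75 | 8% |
| 15% / 15% | 10 / 0 | 1.5 | 17% |
| 15% / 15% | 20 / 0 | 3.0 | 33% |
| 15% / 15% | 10 / 10 or 20 / 20 | 0 | 0% |
| 20% / 10% | 10 / 10 | 1.0 | 11% |
| 20% / 10% | 20 / 20 | 2.0 | 22% |

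**5. The analysis set.** Implementation confirms eligibility before allocation, so eligible may mean everyone randomised, in which case the word adds nothing. The withdrawal rule applies to women who have stopped meeting criteria that they once met, so it can operate after allocation. No section says whether their outcomes are then collected or analysed. Both readings are open.

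**The case against.** The best defence is that this is a condensed article and an analysis plan may exist. Missing-data models and sensitivity analyses commonly sit there, and their absence alone would be no finding. That stands, so the point rests on what the article states: a wrong reason, one named test, and a loosely defined set. The reason might be read charitably as one primary change score per woman, but the promise covering all outcomes in the same section does not fit that reading.

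Several stronger inferences are tempting, and the documents do not support them:

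- *The plan refuses all handling of missing data.* It refuses imputation only. The next sentence allows for drop-out, though vaguely.
- *The plan keeps only a restricted set.* Eligibility is settled before randomisation, and nothing says that withdrawn women's data are removed.
- *Women could be withdrawn because their pain improved.* The pain criterion concerns typical pain at screening and serves as a stratifier. No rescreening is described. Investigators are also blinded, which limits withdrawal that depends on arm, though it does not exclude it.
- *Menstruation 3 scores and partial diaries are discarded.* This is not stated. Daily data also serve secondary outcomes, and no rule excludes a woman who misses one day of three.
- *28 women will be lost.* This is an upper figure. The article does not say when drop-out occurs, and menstruation 2 (day 28) falls about halfway through the intervention.

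It is also fair to say that a likelihood-based model recovers little for a woman lost before menstruation 2 with no later data. Nor does it remove bias when data are missing not at random. Its gain lies in women with partial data and in a stated assumption that a sensitivity analysis can test.

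**Conclusion.** The concern holds in a limited form and should be fixed. The reason for not imputing is false on the article's own description. Complete-case analysis is the default under the only named test, not a declared choice. The intention-to-treat set leaves room for post-randomisation exclusions without requiring them.

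Up to about 28 of 186 women could be missing from the primary test, if all of the planned 15% drop-out falls before the menstruation 2 scores are complete. Bias is possible but not shown. The range of 0.75 to 3 points assumes 15% missing per arm and a 5 to 20 point gap in one arm only; with equal gaps and equal missingness it is zero. A reader might take one of these figures as the expected bias, or as what a better model would remove. Neither inference is supported.

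**What to change.** - Define the intention-to-treat set as all randomised women, analysed as allocated. State that outcome data from women withdrawn or deviating after randomisation are collected where possible and kept in the analysis. Whether such a woman continues the product is a separate clinical matter.
- Delete the single-outcome reason.
- Name one primary analysis in place of the t test, the conditional unbalanced-data models and the Abstract's general description: a likelihood-based repeated-measures model on the three-day pain means at menstruation 1, 2 and 3, with the arm contrast at menstruation 2 as primary.
- Add one missing-not-at-random sensitivity analysis.

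The cost is rewording and modest programming, since the daily scores are already part of the schedule. The downside is a slightly diluted estimate from keeping women who deviate. The sample size need not change. The article reports the trial both as completed in December 2021 (Trial registration) and as recruiting (Trial status), so further data collection may no longer be possible. The analysis set and the model can still be specified.

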### Randomization, sequence concealment, and blinding

This is a double-blind study; the sponsor representatives involved in the study, the investigators, the participants, and any health care professional or site personnel involved in participant management or outcome assessment will remain blinded. Participants will be stratified on their typical abdominal pain score at the beginning of the study and randomized to either the probiotic or placebo supplement in blocks of a pre-specified size. This abdominal pain score will reflect the first 3 days of their typical menstrual cycle and will be on a scale of 3 (mild discomfort) to 7 (very severe discomfort). To maintain a balance in numbers of participants in the main and subgroup studies, randomization will be conducted separately for the main and subgroup studies. Participants will be stratified into two groups including those with mild abdominal pain (score of 3) and those with moderate to very severe abdominal pain (scores 4–7).

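### The primary change score gets an unadjusted t test or a rank test picked on normality; one ANCOVA on data already collected would be more efficient and fixed in advance

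*Protocol article*

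**What the plan says.** The Study outcomes section defines the primary outcome as a change score on the daily VAS: "calculated as the average of the first 3 days of “menstruation 2” when on the intervention minus the average of the first 3 days". The value subtracted belongs to menstruation 1, before the supplement is started.

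The Statistical analysis section gives the test: "The mean delta (difference between pre and post-supplementation) will be tested by parametric or non-parametric" t test, with the choice depending on whether the data look normal. I read the non-parametric version as a two-sample rank test. The section names no covariate and no stratum term. Its one remark on statistical models concerns drop-out.

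The abstract (Methods and analysis) describes the testing of all hypotheses differently: "Two-sided tests using a linear model and a type I error rate of" 0.05.

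The randomisation section uses two factors. First, "Participants will be stratified on their typical abdominal pain score at the beginning of the study", in two groups (score 3; scores 4–7). Second, "randomization will be conducted separately for the main and subgroup studies".

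The Sample size determination section sizes the trial on a mean difference: "A difference of 9 for the change in pain scores between intervention groups". It does so "with an alpha of 0.05 and 80% power". It had no SD of change to work from, so "the standard deviation (19.99) for the final time point was used for the sample size calculation".

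**The concern.** Three things draw attention.

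- **Efficiency.** Subtracting baseline fixes its coefficient at 1. When baseline and follow-up are only moderately correlated, this adds baseline noise to the outcome, whereas ANCOVA estimates the coefficient. Pain stratum was presumably chosen because it should predict pain. Leaving such a factor out of the analysis after stratified randomisation tends to overstate the standard error.
- **An analysis left open.** Whether a t test or a rank test is primary depends on the observed outcome data, and so does the effect measure. A rank test does not estimate the mean difference of 9 points for which the trial is sized.
- **Two descriptions.** The rank branch is not the linear model that the abstract announces.

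What is at stake is power, and a primary result whose form is not settled before the data are seen.

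**Working it through.** **Inputs.** From Sample size determination: difference 9; SDs in the source study 14.52 (baseline) and 19.99 (after one month); two-sided α 0.05 (two-sided from the abstract); 80% power; 79 per arm; 15% drop-out. The correlation r between the menstruation 1 and menstruation 2 means is not in the article. It is an assumption and is shown as a range.

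**Step 1: the plan's own figure.** Standardised difference 9/19.99 = 0.450. The exact two-sample t test needs 78.4, so 79 per arm, and 79/0.85 = 92.9, so 93. The stated size reproduces for an unadjusted t test on change, with 19.99 standing for the SD of change. Power at 79 per arm is 80.3%.

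**Step 2: the two analyses compared.**
- SD of change = √(s₀² + s₁² − 2·r·s₀·s₁)
- ANCOVA residual SD = s₁·√(1 − r²)
- Difference in variance = (s₀ − r·s₁)², which is never negative. With the source SDs it is zero at r = 14.52/19.99 = 0.73.

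Example, r = 0.3 with the source SDs: √(210.83 + 399.60 − 0.6 × 14.52 × 19.99) = √436.28 = 20.89, against 19.99 × √0.91 = 19.07.

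Power at 79 per arm for a difference of 9 (exact two-sample t; the few degrees of freedom used by covariates are ignored):

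| r | SD of change | Change-score t test | ANCOVA SD | ANCOVA |
|---|---|---|---|---|
| *Source SDs 14.52, 19.99* | | | | |
| 0.2 | 22.23 | 71.5% | 19.59 | 81.9% |
| 0.3 | 20.89 | 76.8% | 19.07 | 83.8% |
| 0.36 | 19.99 | 80.3% | 18.63 | 85.5% |
| 0.5 | 17.89 | 88.1% | 17.31 | 90.1% |
| 0.7 | 14.29 | 97.6% | 14.28 | 97.6% |
| *Both SDs 19.99* | | | | |
| 0.3 | 23.65 | 66.2% | 19.07 | 83.8% |
| 0.5 | 19.99 | 80.3% | 17.31 | 90.1% |
| 0.7 | 15.48 | 95.3% | 14.28 | 97.6% |

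**Step 3: what the planning SD guarantees.** 19.99 is a follow-up SD. Under ANCOVA the residual SD cannot exceed it, so power is at least about 80% whatever r is. Under the change-score test it is not a bound. The SD of change equals 19.99 when r = s₀/(2·s₁), which is 14.52/39.98 = 0.363 with the source SDs and 0.5 with equal SDs. Below that r, power falls under 80%.

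**Step 4: the normality switch.** This was simulated under no effect with 79 per arm, 10,000 runs per setting, using a Shapiro–Wilk test at 5% in each arm to choose between t test and rank test. Type I error was 5.0% for normal data and 5.1% for skewed (gamma) data. The switch did not inflate the error rate in these settings.

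**The case against.** The strongest reply is that nothing here is wrong as a test. Comparing change between randomised arms is unbiased, and the sample size agrees with that analysis. If the SD of change really is 19.99, the trial has its stated 80% power. All of that stands.

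A reader might go further than the article allows in four ways:

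- **That the plan ignores baseline pain.** It does not. Baseline enters by subtraction; what is missing is adjustment for it as a covariate.
- **That abstract and body contradict each other outright.** A two-group t test is a linear model with one binary predictor. Only the rank branch conflicts.
- **That the trial is underpowered.** This needs r below about 0.36 with the source SDs. The article gives no r, and the gain from ANCOVA fades to nothing near r = 0.7. The wider gaps come from equal SDs, which is an assumed scenario and not the source study's figures.
- **That the data-driven choice of test inflates false positives.** The simulation does not show it. For skewed data the switch even had more power than the t test (85.2% vs 79.9%, at a shift of 9), though through a test that does not estimate the mean difference.

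The effect of omitting the strata is conservative, and the article has no figure from which to quantify it.

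It can also be said that covariate lists belong in an SAP, which is not shown. Silence alone would indeed be no finding. But the article states the test itself, makes it depend on the data, and describes another method in its abstract, so the point does not rest on silence.

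**Conclusion.** The point holds as a free improvement in efficiency and pre-specification. The planned test is valid, but never more efficient than ANCOVA apart from a few degrees of freedom. With the source SDs the gain is about 10 percentage points of power at r = 0.2, about 5 at r = 0.36 (where the planning SD is exactly right), 2 at r = 0.5 and none at r = 0.7. The larger benefit is robustness: the article concedes that it had no SD of change, and ANCOVA makes the 80% claim hold at any r if 19.99 is right for follow-up.

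Separately, the primary test and effect measure are not fixed before the data are seen, and the rank branch fits neither the abstract nor the sizing.

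These figures assume a linear relation with the same r in both arms and 79 evaluable women per arm. They cover the baseline covariate only, not the strata.

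**What to change.** Name the same single primary analysis in the abstract and in the Statistical analysis section: a linear model (ANCOVA) of the menstruation 2 three-day mean VAS on arm, with menstruation 1 three-day mean VAS, pain stratum (3 vs 4–7) and main study/subgroup as covariates. Report the adjusted mean difference with its 95% CI. Using the change as the response gives the same treatment estimate once the menstruation 1 mean is in the model. Remove the normality-driven choice, and keep a rank test only as a sensitivity analysis.

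The cost is small. All covariates are already recorded, the sample size stays at 79 per arm (93 with drop-out), and three extra terms take 3 of the 156 residual degrees of freedom. The abstract gives both a completion date of December 2021 and a status of still recruiting, so the change should be a dated, documented amendment made before unblinding. If unblinding has already taken place, the adjusted analysis should be reported as supplementary and labelled post hoc.
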